## Introduction

### Background

Twenty per cent of the general population experiences prolonged or recurrent pain for at least 3 months, such pain is then considered to be chronic.^1 2^ Low back pain is the principal cause of years lived with disability and workdays lost in Europe and worldwide,^3^ and its sequelae affect 9% of the global population.^4^ Moreover, although there are several treatment intervention strategies available for patients with chronic low back pain (CLBP), treatment effect sizes have only been moderate.^5^ Such evidence may explain why 40% of the patients are not satisfied with the treatment received.^2^ The economic consequences of chronic pain include direct costs of medical care and pain management treatments, as well as indirect costs of decreased work productivity and sick leave, and of disability and sickness retirement.^2 6^ The indirect costs determine 86%–88% of the total costs produced by patients with CLBP.^7 8^ In particular, in the Netherlands, the costs derived from back pain to Dutch society were 3.5 billion in 2007, corresponding to 0.6% of the gross national product.^8^

In the past decennia, a relevant subsample of patients with chronic pain, including individuals with CLBP, have shown an increased responsiveness to noxious and non-noxious stimuli, described as central sensitisation (CS).^9^ CS is a result of an imbalance in the nociceptive pathways (‘pain pathways’) and supraspinal structures due to an amplified facilitation and/or reduced inhibition.^10–12^ The phenomenon, CS, is manifested by an amplified pain perception regarding its intensity (hyperalgesia and allodynia), duration (aftersensations and temporal summation) and distribution (expansion of the receptive field), as well as a reduced conditioned pain modulation (CPM).^12^ There is currently no gold standard for CS diagnosis. Identifying reference clinical symptoms and signs, however, may indicate the presence of CS: disproportionate pain, diffuse distribution, allodynia and hyperalgesia, hypersensitivity unrelated to mechanical stimulus but rather to environmental sensations (light, temperature, noise or other stressors), maladaptive psychosocial factors and low vagal nerve activity.^13–16^

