Chronic pain is a multifactorial condition which has an impact on physical or body structures and functions, on psychological processes and on daily activities and quality of life of individuals.^2 17 18^ Limited functioning or capacity to perform everyday tasks (essential for an independent living) affects individuals with chronic pain in their mobility and self-care, social relationships, work and leisure.^19^ Individuals’ functioning is composed of body functions (body level)—described by impairments they experience—and of activities and participation (personal and social levels, respectively)—described by capacity and performance tests.^18 20^ An extensive overview of the functioning status is best obtained when the assessment includes suitable and relevant measures from multiple domains of daily living. In particular, lifting capacity, physical activity (PA), aerobic capacity or daily activities participation are measures that account for the multiple operationalisations of functioning in the daily living.

Patients with CLBP are likely to be less physically active, and be more deconditioned and disabled.^3 21–23^ A subsample of patients with CLBP can manifest symptoms and signs of CS being present.^9^ Because patients with CS are more reactive to stimuli and their pain experience is enhanced, the presence of CS and/or higher levels of CS could plausibly be associated with lower physical functioning and participation in patients with CLBP, and vice versa. More severe symptomatology of CS, decreased parasympathetic/vagal activity or altered somatosensory responses have been associated with greater self-reported pain-related disability.^24–30^ However, the associations between altered somatosensory responses and self-reported disability were dependent on the site of testing, the stimuli and the type of tests performed. Also, CS has been assessed with different instruments that measure specific CS clinical symptoms,^12^ lacking a comprehensive assessment of CS in which various reference clinical symptoms are measured together. Moreover, functioning has most frequently been assessed with self-reported disability which is not exclusively representative of the functioning status of the patient.

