### Objective(s)

The objectives of the studies covered by this research protocol are:

To analyse the association between three instruments assessing reference symptoms and signs attributed to CS in patients with CLBP: CSI, QST and HRV.To analyse whether reference symptoms and signs attributed to CS are associated with functioning measurement outcomes in patients with CLBP. Specifically, to analyse the association between the three instruments assessing CS (CSI, QST and HRV) and: lifting capacity, aerobic capacity, PA levels and/or PA distribution or patterns, and patient-reported measurements.To analyse whether changes (between baseline and discharge) in reference symptoms and signs attributed to CS are related to changes in each of the functioning measurement outcomes in patients with CLBP. Specifically, to analyse whether decreases in CS described as: a lower CSI score, an increase in the pain thresholds (QST) and an increase in parasympathetic/vagal tone (HRV) are related to a better functioning described as: an increase in lifting capacity, an increase in aerobic capacity, an increase in PA levels and/or a change in PA distribution or patterns, and better outcome scores in patient-reported measurements.

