*Wind-up ratio* (*WUR*)—to test the nervous system’s painful stimuli temporal summation or responsiveness to repeated noxious stimuli. Such test is assessed with a suprathreshold pinprick stimulator of 256 mN (the PinPrick Stimulator Set, MRC Systems, Germany), which is applied on a single repetition and on a train of 10 repetitions in an area of 1 cm^2^ with intervals of 1 s (wind-up response). The pain intensity measured with an NRS ranging from 0 (no pain) to 100 (most intense pain imaginable) for both the single repetition and the series is recorded in each of the seven body locations (see online supplementary material 1).^50 51^ The WUR (ratio) is calculated as: WUR=(NRS-10/NRS-1). If NRS-1 is 0, the WUR for that location cannot be calculated and it will be registered as a missing value. The WUR test according to the DFNS protocol has shown to have poor test–retest (r=0.67) and interobserver reliability (r=0.56).^44^

*Mechanical detection threshold* (*MDT*)—to test the ability to detect light touch—is assessed with a standardised set of von Frey filaments (OptiHair2-Set, Marstock Nervtest, Germany) with a modified method of limits.^52 53^ Starting at the intensity of 16 mN, the stimulus application progressively decreases until patients do not report any sensation. The intensity of the filament that is not perceived in millinewtons is recorded in each of the seven body locations (see online supplementary material 1).^54^ The MDT test, according to the DFNS protocol, has shown to have good test–retest (r=0.90) and interobserver reliability (r=0.89).^44^

*Pressure pain threshold* (*PPT*)—to test the ability to perceive pressure pain stimuli on muscles—is assessed with an electronic pressure algometer (Force Ten FDX, Wagner Instruments, USA). With this tool, the pressure in the contact point (1 cm^2^ tip) is progressively but steadily increased until patients report to feel pressure change towards painful (burning, drilling or aching). The intensity in newtons when pressure becomes painful and its pain intensity with an NRS ranging from 0 (no pain) to 100 (most intense pain imaginable) scale is recorded in each of the seven body locations (see online supplementary material 1).^32^ The PPT test according to the DFNS protocol has shown to have good test–retest (r=0.88) and interobserver reliability (r=0.84).^44^

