*CPM*—to test the nervous system’s descending pain processing. The CPM test methodology selected for this study follows the recommendations of the EFIC meeting (2013).^55^ The pain modulation is assessed by means of PPT tests (test stimuli) in a distant location from patients’ dominant hand (musculus deltoid and musculus quadriceps of the non-dominant side, see online supplementary material 1) before and after immersing the dominant hand in a bucket full with ice and cold water (cold conditioning stimuli). First, PPT measurements at distant locations are made; then, patients immerse the dominant hand in the bucket for as long as they possibly can with a maximal duration of 3 min; finally, PPT measurements are repeated. The PPT results, intensity in newtons and pain intensity with an NRS ranging from 0 (no pain) to 100 (most intense pain imaginable) scale, in both locations and the time the hand is immersed are recorded. The CPM (%) is calculated as: CPM=[(PPTpost–PPTpre)/PPTpre]∗100, where lower values indicate lower alteration on the nociceptive pathways.^33 43^ The CPM test, as the combination of the PPT handheld algometer and cold stimuli, has shown to be one of the most reliable methods with a modest test–retest reliability (ICC=0.49 and coefficient of variation=63.6%).^56^

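### The stated reading of the CPM score contradicts its own formula and the article's account of central sensitisation, so CPM findings could be read in the wrong direction

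*Protocol article*

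**What the plan says.** In the Quantitative sensory testing section, the CPM test is there "to test the nervous system’s descending pain processing". PPT is measured at two sites away from the dominant hand, before and after that hand is held in ice water. The score is "CPM=[(PPTpost–PPTpre)/PPTpre]∗100", "where lower values indicate lower alteration on the nociceptive pathways". The same section defines the PPT reading: "The intensity in newtons when pressure becomes painful".

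The Background says that CS arises "due to an amplified facilitation and/or reduced inhibition". It lists amplified pain perception among the manifestations, "as well as a reduced conditioned pain modulation (CPM").

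Under Objective(s), objective 3 describes decreased CS on quantitative sensory testing (QST) only as "an increase in the pain thresholds (QST"). It gives no direction for CPM.

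The Analyses section fixes the CSI part A sum score and RMSSD as the other CS variables. It predefines no QST variable. The QST variable is chosen by the strength of its correlation with each functioning outcome.

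**The concern.** The article defines a score and then gives it a meaning that runs against both the arithmetic of the score and the article's own account of CS. That sentence is the only directional rule for CPM in the document, and CPM is the only one of the six sensory tests described as testing descending pain processing. The hypotheses of objectives 2 and 3 are directional: more CS goes with worse functioning, and less CS with better functioning. If the printed rule is applied, failing inhibition is labelled as the less altered state. The conclusion drawn from a CPM association then flips, and checks of model assumptions would not reveal it.

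**Working it through.** There is no stated figure to reproduce. The check is one of sign.

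**Inputs.** The formula, the meaning of PPT and the interpretive sentence come from the Quantitative sensory testing section. The direction of CPM in CS comes from the Background. The PPT values below are assumed for illustration and are not from the article.

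**Step 1: direction of the formula.** CPM = [(PPTpost - PPTpre)/PPTpre] x 100, so dCPM/dPPTpost = 100/PPTpre, which is positive for any positive PPTpre. CPM therefore always rises with the post-stimulus threshold. PPT is the force at which pressure starts to hurt, so a higher PPT means less pain sensitivity.

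**Step 2: numbers, with an assumed PPTpre of 40 N.**

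| PPTpost (N) | Calculation | CPM | Meaning of the threshold change |
|---|---|---|---|
| 52 | (52 - 40)/40 x 100 | +30% | strong inhibition |
| 44 | (44 - 40)/40 x 100 | +10% | some inhibition |
| 40 | (40 - 40)/40 x 100 | 0% | no inhibition |
| 36 | (36 - 40)/40 x 100 | -10% | facilitation |

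**Step 3: the two rankings side by side.** By the Background, reduced CPM, reduced inhibition and amplified facilitation belong to CS, so the bottom row is the most altered and the top row the least. By the CPM sentence, the lowest value is the least altered, so the ranking is exactly reversed.

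**Step 4: what follows if the sentence is applied.**
- CSI against CPM: a negative correlation (more symptoms, weaker inhibition) is agreement under the Background. Under the sentence it would be read as more symptoms with less alteration, that is, disagreement. The same reversal applies to RMSSD.
- Functioning against CPM: a positive association (stronger inhibition, better functioning) supports the hypothesis under the Background. Under the sentence it would count against it.
- Change in CPM: a rise from baseline to discharge is recovering inhibition. Under the sentence it would be read as growing alteration.

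**Step 5: what does not change.** The computed CPM values, correlations, regression coefficients, confidence intervals, p values and explained variance do not use the sentence. Nor does the choice of QST variable, which depends on strength of correlation and not on what the sign is taken to mean.

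**The case against.** **Alteration could mean modulation.** If the word means the change produced by the cold stimulus, the sentence is true. The reading is strained. The Background reports that "altered somatosensory responses have been associated with greater self-reported pain-related disability", and the Participants section lists alterations of sensitivity as a reason for exclusion. In both places the word means abnormality. Even on the kind reading, the sentence would need rewording.

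**The sentence might have been meant for the pain ratings.** A numeric pain rating is also recorded during the CPM test, and a fall in it would indicate inhibition. But the printed formula uses the threshold, not the rating.

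**The sentence is descriptive.** No recoding, cut-off, classification or directional test in the Analyses section uses it, and the Background gives the right direction. This stands, and it limits the point to interpretation. It does not make the sentence right, and no other text corrects it.

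**CPM may never reach a model.** It is one of six tests and is not a predefined proxy. Its reported test-retest ICC is 0.49, against r = 0.67 for the wind-up ratio and 0.80 to 0.90 for the other four. These are different statistics, but low reliability tends to weaken observed correlations. This also stands, and the article gives no basis for a probability that CPM is selected.

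**Conclusion.** The sentence is wrong as written. It contradicts the formula beside it and the Background's account of CS, and this can be shown from the article alone. The size is a complete reversal of the direction of interpretation, with no effect on any computed quantity. It matters on two conditions: that CPM is analysed or selected as the QST variable, and that the printed rule guides the reading.

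A reader might infer that every CPM result will be reported with the wrong sign. The document does not support that, because the formula and the estimates are usable as they stand and the authors could follow their own Background.

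A reader might also infer that objective 1 certainly includes CPM, or that objective 3 itself defines CPM backwards. Neither is stated. Objective 1 takes the CS measurements as its main variables without naming CPM, although its inclusion is likely. Objective 3 speaks only of pain thresholds, and CPM is a percentage change in a threshold. That silence leaves the faulty sentence as the only rule an analyst would have for a change in CPM. It should be corrected before any CPM result is interpreted.

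**What to change.** Replace the interpretive clause with a statement that higher (positive) CPM values indicate stronger pain inhibition, and that lower or negative values indicate reduced CPM, that is, greater alteration of the nociceptive pathways. For objective 3, add that an increase in CPM (%) under the current formula counts as decreased CS.

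Alternatively, reverse the formula to PPTpre minus PPTpost and keep the clause. In that case the signs of CPM coefficients change, and the objective 3 statement must be reversed to match. Only one of the two changes should be made.

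In either case, check that the coding of CPM in the database matches the direction chosen. The cost is a corrected clause, one added statement for objective 3 and a coding check. No new data are needed.

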##### Heart rate variability

The test provides an indication of the function and balance of the autonomic nervous system (ANS), which is responsible for the control of internal functions including self-regulation, adaptability and resilience capacities.^57^ The ANS is susceptible to mental and emotional processes, which in turn can produce an imbalance in self-regulation (affecting, among others, heart rate (HR)) by a hyperactivation of the sympathetic tone and reduced parasympathetic/vagal tone.^15 34^ HRV testing can monitor heart rhythms, or time and pattern variation on HR and interbeat (RR) intervals, and can be used to assess the function of the ANS.^58 59^ The HRV test is performed by assessors trained by the HeartMath Institute, and the 5 minute protocol is executed to guarantee the comparison of the results as recommended by the task force for short-term recordings.^58^ Patients are instructed to sit calmly and breathe normally, while they have an ear pulse sensor placed which is connected to a computer.^60^ The following measures are collected and recorded with the emWave PC software (emWave, HeartMath, Boulder Creek, California, USA): mean HR in beats per minute, mean RR interval in milliseconds; time domain measures in milliseconds as SD of normal-to-normal interval indicator for cyclic components responsible of RR interval variability, root mean square of successive differences (RMSSD) for beat-to-beat variance in HR and parasympathetic/vagal tone; frequency domain measures in ms^2^/Hz as very-low-frequency (0.0033–0.04 Hz) indicator for long-term regulation and sympathetic tone, low frequency (0.04–0.15 Hz) for sympathetic and parasympathetic/vagal tones and high frequency (0.15–0.40 Hz) for parasympathetic/vagal tone related to breathing rate; and normalised coherence indicator for HRV stable or regular pattern over time in percent, where higher scores mean more harmonic signal.

#### Physical functioning measurements

In order to determine the functioning status of individuals with chronic pain in multiple domains, data are obtained from two physical assessments (lifting and aerobic capacity tests), an accelerometer (PA level) and a battery of reported functioning questionnaires.

##### Lifting capacity test

The floor-to-waist lift capacity test is based on the WorkWell Functional Capacity Evaluation (FCE) protocol^61^ and is performed to measure patients’ work functioning or capacity. Such FCE lift test has been shown to have high test–retest (ICC=0.81) and inter-rater reliability (ICC=0.76) in patients with CLBP.^62 63^ Assessors are trained in the floor-to-waist lift capacity test procedure. Patients are given standardised instructions to repetitively lift a crate with weights from a shelf at waist height to the floor and back. The test begins with a weight that can easily be lifted, progressively the load is increased and the test ends when the maximum capacity is reached. The final endpoint can be reached due to: cardiac endpoint (85% of maximum HR), biomechanical endpoint (unsafe increasing weight because of lack of load handling control), patient endpoint (patient decided to stop) and criterion endpoint (normal end of the test).^64^ The maximal load lifted in kilograms is recorded along with the endpoint reason, and the patient-reported and the assessor-observed mechanical effort as measured with Borg’s category ratio (CR-10) scale.^65^ Borg’s CR-10 scale ranges from 0 (at rest) to 10 (very, very hard), and has demonstrated to be a valid visual observation of the effort level of patients during their performance of a lifting capacity test.^66^

##### Aerobic capacity test

The maximal aerobic capacity is assessed with a cardiopulmonary exercise test (CPET). The test is performed with a cycle ergometer (Ergoselect 200p or Ergoselect 200k, Ergoline, Bitz, Germany) following a defined continuous ramp protocol. Before any cycling begins, patients are interviewed about their daily activities, and their resting heart rhythm and function are recorded with an ECG (Assy Cam-14, GE Medical Systems, USA). Patients then have an unloaded warm-up of 3 minutes at 60–70 rotations per minute before the test begins. At the start of the test, an experienced exercise physiologist in discussion with a specialised physician or nurse determines the starting workload (25–100 W) and ramp (5–25 W increase per minute) depending on patients’ estimated fitness level. During the test, patients are asked to maintain a constant cadence while the working load is progressively being increased. Also, they are continuously being verbally encouraged to obtain their maximum performance. The maximal performance is determined by various parameters: a temporary loss of strength and energy (=exhaustion), a plateau in the peak oxygen uptake (VO_2_max), a respiratory exchange ratio higher than 1.15 and/or an HR higher than 85% of the predicted maximal HR.^37^ Overall, the test lasts for 8–12 minutes and throughout the whole assessment patients are monitored on their cardiac activity with an ECG, on their blood pressure with a cuff algometer and on their ventilatory gases on a breath-by-breath basis with a metabolic cart (JAEGER Vyntus CPX, Jaeger, Germany, Hoechberg). The VO_2_max in mL/min and per kilogram in mL/min/kg is collected as the mean of VO_2_ over the last 30 seconds of exercise. Along with VO_2_max, the following measures are collected: peak workload in watts, HR at end of test in beats per minute, breathing frequency at end of test in breaths per minute, expiratory tidal volume in litres, peak energy expenditure in metabolic equivalent of task (MET), test duration in minutes, and the patient-reported and the assessor-observed mechanical effort as measured with Borg’s rating of perceived exertion (RPE) scale. Borg’s RPE scale ranges from 6 (no exertion at all) to 20 (maximal exertion)^65^ and has shown to be highly correlated with HR (r=0.74) and blood lactate (r=0.83),^67^ demonstrating to be a reliable instrument to measure work intensity.

##### PA levels

The objective measurements of PA levels are obtained by means of an accelerometer (ActiGraph GT9X Link, ActiGraph, Pensacola, FL, USA). The accelerometer is a small and light device that monitors wearers’ daily PA and energy expenditure. Participating patients wear the accelerometer attached at their hip level for 1 week continuously during walking hours, in order to ensure the minimum of 4 full-day recordings as recommended by activity monitoring reviewers and experts.^68 69^ Different algorithms are chosen from the software provided by the manufacturer, ActiLife6 (ActiGraph, Pensacola, Florida, USA), to discriminate between low PAs and split patients in three activity intensity categories (sedentary, light and moderate)^70^ and to obtain patients’ energy expenditure in kilocalories^71^ and MET.^72^ The daily and weekly time in hours and percentage of time spent in each of the activity intensity categories as well as the estimated energy expenditure in both kilocalories and MET are collected.

